### 2.3. Setting, participants, and recruitment

#### 2.3.1. Setting.

The study will be conducted at the Queen Mathilde Mother and Child Center, Antwerp University Hospital (UZA), and the Princess Elisabeth Pediatric Hospital, University Hospital Ghent (UZ Ghent). The TP will be implemented over a total period of 16 months, including a post-transfer assessment (see Fig 3).

**Fig 3 pone.0353932.g003:**
[figure not shown]
Overview of the quasi-experimental pre-test post-test study.

Participants in the intervention group will receive the TP over 13–16 months, depending on the trajectory specific to their condition. Questionnaire assessments will be administered at three time points: at baseline, prior to the start of the intervention (T0); at the time of transfer to adult care services (T1), with the questionnaire completed immediately after the last consultation on paediatric care services; and four months post-transfer (T2). For the control group, whom receive usual care, assessments will be conducted at the time of transfer (T1), with the questionnaire completed immediately after the last consultation on paediatric care services, and four months post-transfer (T2).

#### 2.3.2. Participants.

The study will focus on three common chronic childhood-onset conditions: type 1 diabetes, asthma, and obesity. The three diagnostic groups will be included to ensure variability and representativeness. Eligibility criteria for the intervention group include: being 17 years old, having a diagnosis of one of the target conditions, at least one paediatric outpatient visit in the past 12 months, Dutch-speaking, and a planned transfer to adult care within 12 months. Participants in the control group are aged 17,5–18 years, Dutch-speaking, with a planned transfer to adult care in the near term. Patients with severe mental, cognitive, and/or neurological impairments are excluded. At UZ Ghent, only type 1 diabetes patients will be included, while at UZA, patient with asthma and obesity patients will be included.

Based on reference data from previous studies, the intervention target was defined as an improvement in the primary outcome corresponding to a one standard deviation (SD) increase in the TRAQ score [24–26]. This target was set assuming 90% power, an effect size of d < 0.6, and a significance level of α = 0.05. A power analysis conducted using G*Power 3.0 indicated that 22 participants per group (intervention and control) would be required. Considering the heterogeneity of the AYA population and comparable disease complexity across subgroups, this sample size was applied at the population level, resulting in a total required sample of 44 participants. To account for an anticipated attrition rate of 25% over a 24-month follow-up period [27], as well as potential recruitment challenges, the total target sample size was increased to 55 participants. Accordingly, a minimum of 28 participants per group (intervention and control) should be recruited.

For the process evaluation, all participating AYAs, their families, and involved healthcare providers will be invited to complete quantitative assessments. A purposive subsample will be selected for qualitative evaluation to capture variability in experiences and perspectives, ensuring representation across conditions, sites, and roles in the care process.

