### 2.5. Data analysis

#### 2.5.1. Effectiveness.

Baseline characteristics will be summarized using appropriate descriptive statistics (e.g., means and standard deviations or medians and interquartile ranges for continuous variables, and frequencies and percentages for categorical variables). Within the intervention group, pre-post changes over time will be evaluated using paired t-tests or non-parametric equivalents when assumptions are not met. Given the non-randomized and exploratory nature of the study, analyses comparing the intervention and control group will primarily be descriptive and exploratory. Potential baseline differences between groups will be taken into account by exploring propensity score-based approaches, such as inverse probability of treatment weighting (IPTW), if deemed feasible given the sample size and data distribution. Outcome differences between groups will be interpreted cautiously, with emphasis on effect sizes and confidence intervals rather than formal hypothesis testing alone. All statistical tests will be two-sided, and statistical significance will be set at p < 0.05. Missing data will be reported and handled transparently; given the expected small sample size, no multiple imputation procedures are planned.

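### The 90% power for 22 per group belongs to a 1-SD difference between groups; section 2.3.2 words the target as a 1-SD increase and also states d < 0.6, which does not give 22

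*Protocol article*

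**What the plan says.** Section 2.3.2 of the protocol article sets the target as "an improvement in the primary outcome corresponding to a one standard deviation (SD) increase in the TRAQ score". The next sentence reads "This target was set assuming 90% power, an effect size of d < 0.6, and a significance level of α = 0.05". The G*Power calculation then "indicated that 22 participants per group (intervention and control) would be required", "resulting in a total required sample of 44 participants". No comparator is named in the target, and no change under usual care is mentioned.

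Section 2.3.1 (text under Fig 3) gives the intervention group three assessments: T0, T1 and T2. The control schedule starts later: "For the control group, whom receive usual care, assessments will be conducted at the time of transfer (T1", then T2. Section 2.5.1 tests pre-post change in the intervention group only and treats the comparison with controls as mainly descriptive and exploratory. It adds: "All statistical tests will be two-sided, and statistical significance will be set at p < 0.05".

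**The concern.** An increase and an improvement describe change over time in the patients who receive the programme. A sample size given for intervention and control describes a contrast between groups. These are different quantities, and section 2.3.2 moves from one to the other without saying so.

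The gap matters here because controls are not measured at T0. Their change up to transfer can be neither estimated nor subtracted, so the between-group contrast is one of levels at T1 or T2. By then controls have had their own paediatric care and are approaching or at 18 years. They may be readier than the intervention group was at 17. The programme could then meet a 1-SD improvement in full while the between-group difference falls short of 1 SD, and the stated 90% would not describe the study's chance of detecting it.

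The stated effect size below 0.6 adds a second, plainer conflict in the same paragraph, because it does not lead to 22.

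**Working it through.** **Inputs.** From section 2.3.2: a 1-SD target, power 0.90, alpha 0.05, d below 0.6 and 22 per group. From section 2.5.1: two-sided tests. From section 2.3.1: controls assessed at T1 and T2 only. Not given, and so assumed below: how far controls at T1 differ from the intervention group at T0.

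**Step 1: reproduce the 22.** For two independent means, n per group ≈ 2(z₀.₉₇₅ + z₀.₉₀)²/d².
- At d = 1.0: 2(1.960 + 1.282)²/1 = 21.0, which rounds up to 22. The exact t-test gives 22.02, and power at 22 per group is 0.900.
- At d = 0.6: 21.0/0.36 = 58.4, so 59. The exact t-test gives 60 per group. A smaller d needs more.

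**Step 2: try other routes to 22.**

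| Test | d = 1.0 | d = 0.6 |
|---|---|---|
| Two-sample t, two-sided, per group | 22 | 60 |
| Two-sample t, one-sided, per group | 18 | 49 |
| Paired t, two-sided, total | 13 | 32 |
| Paired t, one-sided, total | 11 | 26 |

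Of these, only the two-sided two-sample test at d = 1.0 gives 22. A group-by-time interaction (f = 0.25, correlation 0.5, two measurements) also gives 44 in total at power 0.900, but it too encodes a 1-SD between-group difference, in that case a difference in change. So the 90% belongs to a 1-SD difference between groups. A paired test of a 1-SD change would have needed 13 patients.

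**Step 3: what the design can contrast.** Let I₀ and I₁ be the intervention means at T0 and T1, and C₁ the control mean at T1, in SD units. Then

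I₁ − C₁ = (I₁ − I₀) − (C₁ − I₀).

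If the target is met as the intervention group's own gain, I₁ − I₀ = 1 and the contrast is 1 − (C₁ − I₀). It equals 1 SD only if C₁ = I₀. The term C₁ − I₀ combines two things: the controls' gain under usual care, and any starting difference from allocation by age. The study can separate neither, because controls have no T0.

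**Step 4: power at smaller net differences.** Two-sided two-sample t-test, 22 per group, 42 degrees of freedom, noncentrality d√(22/2) = 3.317d.

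| Net difference (SD) | Noncentrality | Power, 22 per group | n per group for 90% |
|---|---|---|---|
| 1.0 | 3.317 | 0.900 | 22 (22.02) |
| 0.9 | 2.985 | 0.830 | 27 |
| 0.8 | 2.653 | 0.736 | 34 |
| 0.7 | 2.322 | 0.621 | 44 |
| 0.6 | 1.990 | 0.494 | 60 |

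Power drops below 80% once C₁ − I₀ exceeds about 0.14 SD, that is, at a net difference below about 0.86.

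**Step 5: the recruited number.** The 28 per group is the attrition allowance. If nobody were lost, power would be 0.911, 0.836, 0.730 and 0.597 at net differences of 0.9, 0.8, 0.7 and 0.6.

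**The case against.** The strongest reply is that section 2.3.2 never says the 1 SD is the intervention group's own change. The sentence could be a loose description of the advantage sought over control. A two-sample calculation at d = 1.0 would then be the right one, and no condition on C₁ would arise. This stands as a possible reading. A reader might infer that the plan definitely entered a within-group gain as a between-group difference, so that 90% power holds only if usual-care patients gain nothing. The documents do not support that. The wording leans that way but does not settle it, and the exact condition is C₁ = I₀, which also depends on starting levels. Section 2.3.3 itself acknowledges possible age-related differences between groups.

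Second, every value of C₁ − I₀ is assumed, and any sample size loses power when the true difference is smaller than planned. That is also true. The figures show sensitivity and do not predict what the study will find.

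Third, section 2.5.1 makes the group comparison mainly exploratory, with emphasis on effect sizes and confidence intervals, and the Discussion disclaims definitive conclusions on effectiveness. A reader might fear that a non-significant contrast will be reported as proof of no benefit, but these statements largely guard against that. They do not say what the 90% refers to, and they leave it standing beside an effect size it does not match.

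Fourth, the 0.6 might be the intended between-group effect and the 22 the error. The documents do not say which figure is wrong. For that reason the two must be reconciled together; one cannot simply be assumed to be a slip.

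**Conclusion.** The point holds as an ambiguity with a measurable consequence. The number 22 reproduces exactly as a 1-SD between-group difference and by no calculation tried at 0.6, where power with 22 per group is 49%. The target is worded as an increase, and the design cannot turn an increase into a between-group difference without knowing C₁ − I₀. If the 1 SD is the intervention group's own gain, power for the available contrast is 83%, 74%, 62% or 49% at net differences of 0.9, 0.8, 0.7 or 0.6 SD. If it was meant as an advantage over control, the 90% is right for that quantity, but the wording and the 0.6 still need correcting.

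The figures rest on 22 evaluable per group, a common SD, a two-sided 0.05 test and an unadjusted comparison at T1. The practical effect is limited to the stated power and to how a wide confidence interval will be judged. Data collection and the planned analyses are unaffected.

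**What to change.** In section 2.3.2:

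1. State that 22 evaluable participants per group give 90% power for a between-group TRAQ difference of 1.0 SD at T1, net of any usual-care gain and any age-related starting difference.
2. Replace the effect size below 0.6, or reconcile it with 22 per group. If 0.6 is the between-group effect intended, state the power as 49%.
3. Give the power at smaller net differences, for example 74% at 0.8 SD and 49% at 0.6 SD, and say that the documents hold no estimate of the usual-care gain.
4. Do not present the 90% as power to confirm the 1-SD pre-post improvement against control.

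The cost is wording only, with a less favourable stated power. No patients, visits or analyses are added, so the change can still be made although section 2.1 reports that recruitment ran to March 2026.

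### Sample size: 22 per group does not follow from 90% power and d < 0.6; it matches d = 1.0, and power at d = 0.6 is about 49%

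*Protocol article*

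**What the plan says.** The whole sample-size argument is in section 2.3.2 (Participants) of the protocol article.

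- Target: "an improvement in the primary outcome corresponding to a one standard deviation (SD) increase in the TRAQ score".
- Assumptions: "This target was set assuming 90% power, an effect size of d < 0.6, and a significance level of α = 0.05".
- Result: "A power analysis conducted using G*Power 3.0 indicated that 22 participants per group (intervention and control) would be required".

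The 44 participants this gives are then raised for attrition to 55 in total, with at least 28 per group. Section 2.5.1 fixes the sidedness: "All statistical tests will be two-sided, and statistical significance will be set at p < 0.05". Section 2.3.2 does not name the test used in the power run and gives no correlation between repeated measurements.

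**The concern.** An increase of one SD is d = 1.0. The next sentence gives an effect size below 0.6. Required sample size varies roughly with 1/d², so moving from 1.0 to 0.6 multiplies it by about 1/0.36 = 2.8. One figure of 22 cannot serve both.

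This paragraph is the only justification of the sample size for the primary outcome. A reader who accepts it will believe the study has 90% power for differences of 0.6 SD or less. A non-significant or imprecise TRAQ result could then be read as evidence against a moderate effect, when the study had about an even chance of missing one.

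**Working it through.** **Inputs.** Alpha 0.05, power 90%, d < 0.6, the one-SD target and 22 per group come from section 2.3.2. Two-sided testing comes from section 2.5.1. Allocation is 1:1. For d < 0.6 I use 0.6, the limit most favourable to the plan.

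**Step 1: reproduce the stated 22.** The normal approximation for two independent means is n per group = 2(z₀.₉₇₅ + z₀.₉₀)²/d² = 2(1.960 + 1.282)²/d² = 21.02/d².

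- d = 1.0: 21.02, rounded up to 22.
- d = 0.6: 21.02/0.36 = 58.4, rounded up to 59.

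The exact calculation uses the noncentral t distribution with 2n − 2 degrees of freedom and noncentrality d√(n/2). It gives n = 22.02 at d = 1.0 and n = 59.35 (60) at d = 0.6. So 22 reproduces from the one-SD target and not from d = 0.6. Strict rounding of 22.02 gives 23, but power at 22 is 89.97%, so the difference is immaterial.

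**Step 2: power the design actually has** (two-sample t-test, two-sided alpha 0.05). With 22 per group and d = 0.6, the noncentrality is 0.6 × √11 = 1.99, just under the critical value t₀.₉₇₅,₄₂ = 2.02. Power is therefore close to one half.

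| Evaluable per group | Power at d = 0.6 | d detectable with 90% power |
|---|---|---|
| 21 (28 less 25%) | 47% | – |
| 22 | 49% | 1.00 |
| 28 (no losses) | 60% | 0.88 |
| 60 | 90% | 0.6 |

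Below 0.6 the gap widens: d = 0.5 needs 86 per group, and 22 per group have 37% power.

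**Step 3: other readings of d = 0.6 at 90% power.**

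- One-sided two-sample t-test: 49 per group.
- Paired t-test with 0.6 as the standardised mean change: 32 pairs two-sided, 26 one-sided. With 22 pairs, two-sided power is 77% and the smallest standardised change detectable with 90% power is 0.725.
- Rank tests need more than the corresponding t-tests.

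None gives 22.

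**Step 4: precision.** The expected half-width of the 95% confidence interval for a between-group difference, in SD units, is t₀.₉₇₅ × √(2/n). For n = 22 it is 2.02 × 0.302 = 0.61. For n = 28 it is 2.00 × 0.267, about 0.54.

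**The case against.** Three arguments can be made for the plan.

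**Other inputs can give 22.**

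- A one-sided two-sample test at d = 0.9 needs 21.9 per group. Section 2.5.1 makes all tests two-sided, and 0.9 appears nowhere in the article.
- A paired test with d = 0.6 in raw SD units has a standardised change of 0.6/√(2(1 − r)). At r = 0.66 that is about 0.73 and needs 22 pairs. The correlation is not stated, and a one-group test does not fit a number given for each of intervention and control.
- ANCOVA with a baseline correlation near 0.8 needs about 22 per group. Again the correlation is not stated, and section 2.3.1 gives the control group no T0 measurement.
- A two-time-point repeated-measures interaction with f = 0.3 and correlation near 0.3 needs 44 in total. The article names neither that analysis nor those inputs.

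What stands is that the article cannot prove what was entered in G*Power. None of these routes makes the paragraph correct as printed.

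**The study is exploratory.** Section 2.5.1 calls the between-group comparisons primarily descriptive and puts the emphasis on effect sizes and intervals. The Discussion disclaims definitive conclusions on effectiveness. This limits the harm, since no confirmatory claim depends on the 90%. It does not correct a false power figure, and the Discussion also intends to use the preliminary effect sizes to design a larger trial.

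**A rewritten sentence might credit the authors with a calculation they did not make.** This is a fair caution. It is met by labelling the new text as a correction and stating what the achieved sample size delivers, which is true whatever was originally run.

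**Conclusion.** The concern holds. Section 2.3.2 attaches two incompatible effect sizes to one sample size, and the one presented as the power assumption does not produce it. For a two-sided two-sample t-test at alpha 0.05 with equal groups, 90% power at d = 0.6 needs 60 per group, about 2.7 times the stated 22. The stated number has about 49% power at d = 0.6 and 90% only at about d = 1.0.

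These figures assume independent groups, equal variances and no baseline adjustment. The last assumption fits a control group without T0. A different test with a documented correlation could change them, but the article gives neither. The point must be corrected because the stated power is one the design does not deliver.

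**What to change.** Remove d < 0.6 from section 2.3.2 and restate the calculation, for example: 22 evaluable participants per group give 90% power (two-sided alpha 0.05, two-sample t-test) for a between-group difference of 1.0 SD in TRAQ; power is about 49% for a difference of 0.6 SD. Add that the expected 95% confidence interval half-width is about 0.6 SD, which suits the estimation emphasis of section 2.5.1.

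Check the wording against the saved G*Power record. If another test was used, name it and report its effect size, sidedness and any correlation, and still give the two-sample power figures for the between-group comparison. Because section 2.1 places the end of recruitment in March 2026, label the text as a correction made after recruitment closed.

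The cost is a few sentences. No participants are added and no analysis changes. The stated sensitivity of the study becomes less favourable.

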#### 2.3.3. Recruitment.

Recruitment of AYAs will be facilitated through paediatricians at the participating hospitals. Potentially interested paediatric care teams will first be identified using convenience sampling, based on their prior involvement in the initial COCCOS work package. These teams will be invited to attend an informational session during their regular team meetings, where researchers will present the study objectives and procedures, address questions, and invite teams to participate. Participating paediatricians, or their hospital/department administrative staff, will subsequently identify eligible patients based on predefined inclusion criteria. Eligibility will primarily be determined by the age of the AYA, which will also define allocation to either the intervention or control group based on predetermined age criteria. This pragmatic approach reflects real-world transition practices, where transfer to adult care is primarily age-driven. Although this may introduce potential selection bias due to age-related differences between groups, it enhances the ecological validity of the study by mirroring routine care pathways. During routine consultations, paediatricians will briefly introduce the study to eligible AYAs and their parents and invite them to participate. AYAs who express interest will be referred to a member of the research team present at the hospital department. The researcher will provide detailed written and verbal information about the study, answer any remaining questions, and guide both the AYA and their parents through the informed consent process.

### 2.4. Data collection

#### 2.4.1. Effectiveness.

A questionnaire is developed based on the existing literature and includes several validated instruments:

**Transition Readiness Assessment Questionnaire (TRAQ), version 6.0.** As the primary aim of the TP is to prepare AYAs for transition to adult care, the primary outcome is transition readiness. This is assessed using the TRAQ (version 6.0) [25,26,28]. The TRAQ is a 20-item self-report instrument designed to evaluate the skills necessary for a successful transition. It covers four domains: (1) medication management, (2) appointment keeping, (3) tracking health issues, and (4) talking with providers. In addition, it includes two global transition readiness items. Items are scored on a 5-point Likert scale, with total scores ranging from 0 to 53, where higher scores indicate greater transition readiness [28]. Prior to use in this study, the TRAQ will be forward-backward translated into Dutch (Flemish) to ensure linguistic and cultural validity (REF TRAQ).

**Gothenburg Young Persons Empowerment Scale (GYPES).** Patient empowerment is assessed using the GYPES [29], a validated 15-item instrument specifically developed for young people with chronic conditions. The instrument captures multiple domains of empowerment, including knowledge and understanding of one’s condition, personal control, identity, shared decision-making, and the ability to enable others. Responses are scored on a 5-point Likert scale, with higher scores reflecting greater levels of empowerment. The GYPES provides insight into how confident AYAs feel in managing their health and engaging in care.

**Medication Adherence Report Scale (MARS-5).** Medication adherence is evaluated using the MARS-5 [30,31], a brief 5-item measure assessing both intentional and unintentional non-adherent behaviours. Items address behaviours such as forgetting to take medication or deliberately altering doses. Each item is rated on a 5-point Likert scale, with higher scores indicating better adherence. The MARS-5 is widely used due to its simplicity and sensitivity to different types of non-adherence.

**EQ-5D-5L.** Self-perceived health status is measured using the EQ-5D-5L [32], a standardised instrument covering five dimensions (mobility, self-care, usual activities, pain/discomfort, and anxiety/depression). Each dimension is rated across five levels of severity, ranging from no problems to extreme problems. Responses define a specific health state that can be converted into a utility score using country-specific value sets. Additionally, it includes a visual analogue scale (VAS), where AYAs to rate their overall health on a scale from 0 (worst imaginable health) to 100 (best imaginable health).

**Hospital Anxiety and Depression Scale (HADS).** Symptoms of anxiety and depression are assessed using the HADS [33], a 14-item instrument designed for use in clinical populations. It consists of two subscales: anxiety (seven items) and depression (seven items). Each item is scored on a 4-point scale, resulting in subscale scores ranging from 0 to 21. Higher scores indicate higher levels of anxiety or depressive symptoms. The HADS is commonly used because it focuses on psychological symptoms while minimizing the influence of physical illness.

At baseline, data will be collected using a paper-based questionnaire. This approach allows the researcher to be present during completion, providing clarification and support in case participants experience difficulties or have questions. At subsequent time points, questionnaires will be administered electronically via a secure online survey platform (i.e., REDCap) and distributed through an automated email system. To maximize response rates, reminder emails will be sent to participants who have not completed the questionnaire within a predefined timeframe. The questionnaire was pilot tested internally by the research team to evaluate its feasibility and acceptability. Specifically, the pilot evaluation focused on readability, comprehensibility of the items, and overall completion time. On average, completion of the questionnaire takes approximately 10–15 minutes, indicating an acceptable respondent burden.

